### Safety

An important consideration for any program that delivers an exercise prescription or recommendation via the internet is ensuring participant safety. Information about how to perform the prescribed exercises and general tips for safe exercising are available on the Web portal. In addition, we have attempted to minimize the risk of adverse events during exercise by excluding men who may be at risk because of their current health status and/or prostate cancer treatment, unless they receive clearance from their physician to participate in moderate intensity exercise. In addition, the generated exercise prescription takes into account a man’s current health status, including whether or not he is currently receiving treatment for his prostate cancer with surgery, radiation or chemotherapy, ADT, or immunotherapy. For example, any man currently in active treatment is prescribed a low-intensity exercise program, regardless of other health indicators. If a man has no health indicators that dictate that he receives a low-intensity exercise program, the intensity of exercise is prescribed based on his self-reported baseline exercise levels so that the program is safe and effectively provides a sufficient stimulus for adaptation.

**Figure 2 figure2:**
[figure not shown]
Example of the assessment and feedback that will be provided to a participant about how well he meets the dietary recommendations in the Community of Wellness.

**Figure 3 figure3:**
[figure not shown]
Example of a Level 4 “Dashboard” to help men navigate to different elements of the portal.

### Outcome Measures

We will evaluate acceptability and feasibility of the Community of Wellness intervention after 3 months via surveys, usage analytics from the Web portal, and focus groups. We will also assess study retention percentage of participants completing surveys) at 3 and 6 months as a reflection of acceptability and feasibility. Secondarily, we will explore the effectiveness of the different levels of the intervention on self-reported changes in diet or physical activity habits, QoL, and self-efficacy after 3 months and 6 months. To describe characteristics of our sample, we also ask men to self-report sociodemographic information (ie, age, race/ethnicity, marital, and employment status) and their cancer and health histories using an in-house questionnaire designed for this study.

#### Acceptability and Feasibility

To assess acceptability and feasibility of the Web-based intervention levels, we will evaluate accrual, participant retention, and adherence. We will measure accrual as the percentage of the target sample enrolled within a 1-year recruitment period. We expect to enroll the full sample (n=200) within this time frame. We will also collect information to allow us to determine the feasibility of recruitment, for example, percentage of men eligible and percentage of men enrolled out of the total contacted about the study. We will measure retention as the percentage of participants who complete postintervention and postfollow-up surveys out of the total sample. We expect to retain 80% of the full sample postintervention (n=160) and 80% of the postintervention sample (n=128) at follow-up. We will measure adherence as the number of times a man accesses the Web portal during the intervention period (quantified as the number of log-ins). We expect 100% of men to adhere to a single log-in and that the number of log-ins will significantly differ across levels, with Level 1 having the lowest and Level 4 having the highest adherence. We will measure the technical usage statistics for the Web portal, including frequency of log-ins, individual page views, and access of exercise videos. Post intervention, participants in each level are also asked to assess their use and the helpfulness of the Web portal, its components, and other study tools through an online survey.

#### Adherence to Diet and Exercise Recommendations

To estimate the effect of the intervention on behavior change, we will compare item-level data (eg, minutes per week of moderate activity, minutes per week of vigorous activity, and servings per week of cruciferous vegetables) at baseline and 3 months from the Community Healthy Activities Model Program for Seniors (CHAMPS) physical activity survey [65,66] and a validated FFQ [67]. We will examine behaviors overall as part of a “behavior score” (see below) and with a focus on activities and dietary components that correspond to our recommendations.

The CHAMPS survey is administered at baseline, 3 months, and 6 months. This validated survey estimates total weekly energy expenditure (in kilocalories per week) from physical activities for older adults. The 41-item questionnaire asks about recent engagement in specific types of vigorous-, moderate-, and light-intensity activities per week and the frequency and duration of participation. Specific items can be categorized as aerobic or resistance exercise, and responses to these items will be evaluated to determine how closely a man complied with his prescribed training program. In addition, we can calculate weekly energy expenditure in moderate- and/or vigorous-intensity activities separately for comparison with other studies.

The validated Harvard TH Chan School of Public Health FFQ for adults from 2007 is administered at baseline, 3 months, and 6 months [68]. This 132-item survey assesses dietary intake in categories from “never or less than once per month” to “6 or more times per day.” The original survey asks about intake over the past year; we modified the survey for this study to ask about intake over the last month.

In addition to the responses to standard surveys, participants who receive technology support (Levels 3 and 4) complete weekly online surveys to report their progress toward meeting their exercise and diet recommendations. Participants report the number and type (eg, aerobic or resistance) of exercise sessions, average session duration, and exercise intensity. Men also report which of the recommended dietary habits they worked on, if they met any of diet goals, and which goals were the most challenging. This type of charting is used to provide another form of behavioral support; we can also use the data to further evaluate adherence to recommendations.

We will calculate a “behavior score” based on how well each participants’ self-reported diet and exercise habits match the 8 dietary and 3 exercise recommendations. For each of the 11 targeted behaviors, participants will be assigned 0 points if they do not meet that recommendation, 1 point if they almost meet the recommendation, and 2 points if they meet the recommendation. The overall score ranges from 0 to 22, with higher values indicating closer adherence to the exercise and diet recommendations. To calculate the score, a priori numeric criteria were defined for not meeting, almost meeting, or meeting each of the 11 recommendations. These criteria were used in the design of the intervention to provide tailored feedback to participants randomly assigned to Levels 2 or above. For example, the recommendation for fish was to consume 2 or more servings per week. Men consuming less than 1 serving per week are considered “not meeting” the recommendation and receive 0 points toward the composite score; men eating more than 1 serving per week but less than 2 servings per week are considered “almost meeting” and given 1 point; and those eating more than 2 servings per week are “meeting the recommendation” and given 2 points. We will examine mean scores for each group at baseline and 3 months and changes in scores from baseline to 3 months. The development and application of a behavior score like this comes from literature examining healthy lifestyles and risk of chronic disease. For example, members of our team previously reported the development and validation of a lifestyle score for the prevention of lethal prostate cancer, which incorporated several of the diet and exercise components recommended in this study [69].

Other “healthy lifestyle” scores, computed similarly, have been developed and shown to be useful for summarizing lifestyle-disease relationships in other disease areas, such as hypertension or cardiac death [70,71].

To assess adherence to use of technology support via physical activity tracking devices for men in Levels 3 or 4, we will assess the number of days they wore their wearable device during the study period. We will also consider data from the wearable device to describe the average number of steps taken per day, active minutes per week, and miles covered per week.

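### The printed fish scoring rule gives no points category to exactly 1 or exactly 2 servings per week, and its top cut contradicts the stated recommendation

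*Protocol article*

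**What the plan says.** The behavior score is defined in the Protocol article under Adherence to Diet and Exercise Recommendations. Each of 11 behaviors (8 dietary, 3 exercise) earns 0 points if the recommendation is not met, "1 point if they almost meet the recommendation, and 2 points if they meet the recommendation". For the total, "The overall score ranges from 0 to 22".

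The article states that "a priori numeric criteria were defined for not meeting, almost meeting, or meeting each of the 11 recommendations", and that these criteria also shaped the tailored feedback given at Level 2 and above. Only fish is printed, as an example:

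- Recommendation: "the recommendation for fish was to consume 2 or more servings per week".
- 0 points: "Men consuming less than 1 serving per week are considered" not meeting.
- 1 point: "men eating more than 1 serving per week but less than 2 servings per week are considered" almost meeting.
- 2 points: "those eating more than 2 servings per week are" meeting.

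Intake comes from the food frequency questionnaire: "This 132-item survey assesses dietary intake in categories from" less than monthly up to several times per day.

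Statistical Power calls behavior change, measured by this score, the secondary outcome and gives it a power calculation. Proposed Statistical Analyses puts the three-way classification first among the behavior analyses, followed by intakes as continuous variables.

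**The concern.** A scoring rule has to place every possible answer in exactly one category, and its top category has to agree with the target it scores. The printed fish rule fails on both counts, and it fails at the whole numbers 1 and 2. Those values are plausible because intake is recorded in frequency categories and the target is itself a whole number.

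A programmer who follows the text has to improvise for these men: move them down a category, score them 0, or set the item to missing. Two analysts could score the same answers differently. The score is also the only behavior outcome with a power calculation. If the portal uses the printed cuts, a man at exactly the recommended intake might be told that he falls short, or might get no classification.

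**Working it through.** **Inputs.** All come from the Protocol article. From Adherence to Diet and Exercise Recommendations: the fish target x ≥ 2; the printed categories x < 1, 1 < x < 2 and x > 2; and 11 items of 0 to 2 points. From Statistical Power: 50 men per group, mean changes of 2 and 4.85 points, SD 5, two-sided alpha .05, 80% power and effect size 0.57.

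**1. The plan's own figures.**
- Range: 11 × 0 = 0 to 11 × 2 = 22, as stated.
- Effect size: (4.85 − 2)/5 = 2.85/5 = 0.57, as stated.
- Power, normal approximation: 0.57 × √(50/2) = 2.85; 2.85 − 1.96 = 0.89; Φ(0.89) ≈ 81.3%. The two-sample t-test gives 80.6%. The stated figure of 80% is reproduced.
- Detectable effect size at 80% power (t-test): 0.566, against the stated 0.57.

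None of these inputs depends on the fish cut points, so correcting the cuts leaves the power statement unchanged.

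**2. The printed rule, applied literally.**

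| Servings per week | Printed rule | Closed lower bounds |
|---|---|---|
| 0, 0.5, 0.99 | 0 | 0 |
| exactly 1 | no category | 1 |
| 1.01, 1.5, 1.99 | 1 | 1 |
| exactly 2 | no category | 2 |
| 2.01, 3 | 2 | 2 |

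No other section of the article assigns the two missing values.

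**3. Effect on one man.** At exactly 2 servings he meets the target, so the general rule gives 2 points. He loses 2 − 1 = 1 point if treated as almost meeting, 2 − 0 = 2 points if scored 0, or the whole item if it is set to missing. At exactly 1 serving, scoring 0 rather than 1 costs 1 point.

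**4. Effect on the comparison between arms.** Let L be the points lost by a man at the boundary and p the proportion of men there. The difference in mean change then shifts by

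−L × [(p at 3 months − p at baseline) in the intervention arm − (p at 3 months − p at baseline) in Level 1].

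The article gives no value of p. Three assumed cases, for fish only:
- Equal change in p in both arms: the shift is 0.
- No one at the boundary at baseline; 30% of the intervention arm and 10% of Level 1 there at 3 months; L = 1: the shift is −1 × (0.30 − 0.10) = −0.2 points, and 0.2/2.85 ≈ 7% of the planned difference.
- The same proportions with L = 2: −0.4 points, or about 14%.

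Exchanging the two arms' proportions reverses the sign. These cases show scale only and are not estimates.

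**The case against.** The strongest reply is that this is loose wording in an illustration. The governing sentence gives 2 points for meeting a recommendation, and the fish recommendation includes exactly 2, so on a fair reading exactly 2 earns 2 points and only exactly 1 is truly open. The working criteria may be correct in the code. The outcome is secondary in a pilot, and fish intake is also to be analyzed as a continuous variable, which needs no cut points.

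Much of this stands. It limits the seriousness, and it means that faulty scoring or feedback cannot be presumed. It does not remove the defect. The explicit cut still contradicts the general rule in the same paragraph, exactly 1 has no category under either reading, and the article gives no means of telling which version was implemented. Nor is this a detail left to a fuller document, since the article chose to print the numeric criteria.

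Stronger readings are tempting but unsupported:
- **All 11 items share the fault.** A reader might assume 10% to 30% of men at a cut point, 1 point lost each, and multiply by 11 to get 1.1 to 3.3 points against the planned 2.85. Ten of the 11 criteria are not shown, the percentages have no source, and the sum sets a loss in score level against a between-arm difference in change.
- **The error pulls the arm difference toward zero.** Men advised to eat 2 servings might cluster at exactly 2. But Level 1 also receives the diet guidelines, men may sit at a boundary at baseline, and the conversion from questionnaire category to servings is not given.
- **The trial's power or main result is at risk.** The primary outcomes are accrual, recruitment and retention, with their own precision statement.

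**Conclusion.** The point holds for the fish item as printed: exactly 1 and exactly 2 servings per week are unscored, and the cut above 2 conflicts with both the recommendation and the general scoring rule. The loss is up to 2 points of 22 for a man at exactly 2. It is up to 1 point for a man at exactly 1, if that value is meant to count as almost meeting, which the article does not settle. How many men are affected, and the direction of any bias between arms, cannot be determined from the article. The primary outcomes, the 0 to 22 range and the stated 80% power are unaffected. This is a minor correction to a secondary outcome's definition.

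**What to change.** Restate the fish categories so that they are exhaustive and agree with the recommendation: x < 1 scores 0; 1 ≤ x < 2 scores 1; x ≥ 2 scores 2. The upper bound follows from the article's own target. Placing exactly 1 in the middle category applies the same convention, and the team should confirm that it is what was intended.

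Then check the a priori criteria for the other 10 items, the scoring code and the portal feedback against the reconciled boundaries. Self-Efficacy for Physical Activity and Diet gives a cooked-tomato target of the same form (2 or more servings per week), so that item is a natural place to begin. Re-score stored answers only if the faulty boundaries were actually used.

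The cost is one corrected sentence and a short check of criteria and code, with a re-run of the scoring at most. No new data are needed, and because enrollment was ongoing when the article was written, the definition could be settled before the final analysis.

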#### Fatigue and Sleep Quality

Fatigue and sleep quality are assessed using validated instruments at baseline, 3 months, and 6 months. The Patient Reported Outcome Measurement Information System 7-item Short Form-Fatigue questionnaire [72] is used to assess changes in cancer-related fatigue. The Pittsburgh Sleep Quality Index is used to assess changes in sleep quality [73,74].

#### Self-Efficacy for Physical Activity and Diet

Self-efficacy for physical activity will be measured with a standard 6-item questionnaire at baseline, 3 months, and 6 months [75]. Self-efficacy for diet will also be collected at 3 and 6 months using a similar approach by having participants rate their confidence in performing each recommended task (eg, consume 2 or more servings of cooked tomatoes per week) using a Likert scale. We will evaluate whether baseline self-efficacy predicts response to the intervention arms and whether the interventions improve self-efficacy for physical activity and diet compared with control.

#### Stage of Change for Physical Activity

The Physical Activity Stage Assessment is a 5-item measure of a person’s readiness to engage in recommended levels of physical activity and has been used in prior studies of cancer survivors [47]. We will evaluate the influence of the behavioral support on readiness to engage in physical activity.

#### Focus Groups

Focus groups will be conducted post intervention to evaluate elements of usability and acceptability that will provide greater depth of information beyond what can be obtained via surveys. Focus group participants will be recruited from each of the different levels of intervention, to gain insight into participant experience at each of the levels. Focus groups will be conducted by phone so that we do not exclude participants who cannot travel to each study site. There is not an a priori selection of the focus group subsample; rather, we will examine the demographic data once each site is fully enrolled and contact a representative sample from the study population based on age, race/ethnicity, disease stage, time since diagnosis, and intervention arm.

### Statistical Considerations

#### Statistical Power

The primary outcomes for this pilot are acceptability and feasibility, as assessed by percent accrued in 1 year, percent recruited out of total contacted, and retention at 3 months. We anticipate enrolling 100% of the target 200 in 1 year, enrolling 3% of the total sample contacted via mass mailings, and retaining 80% of participants at 3 months. With 200 participants, we will be able to identify a retention proportion of 80% at 3 months (95% CI limits 74.5%-85.5%) and should be able to identify the other more extreme proportions with higher precision and tighter confidence limits. We will also assess the proportion completing surveys at 6 months, secondarily. If we assume 160 individuals complete the 3-month surveys, then we will have 80% power to detect a retention proportion at 6 months of 80% with a 95% confidence limit of 73.8% to 86.2%.

For the secondary outcome of behavior change, we will compute a composite *behavior score* at baseline and 3 months based on the self-reported survey data and as described above. With 50 participants per group, there is 80% of power to detect an effect size of 0.57 at a 2-sided alpha of .05 when comparing the change in score from baseline to 3 months for an intervention group (either Levels 2, 3, or 4) compared with the reference group (Level 1). For example, assuming on average men in the reference group (Level 1) experience a 2-point increase in scores from baseline to 3 months, 50 participants in Level 1 and 50 participants in Level 2 would provide power of 80% or higher if there is an average increase of 4.85 points or greater in Level 2, with an SD of 5. As a pilot study, multiple testing adjustments were not accounted for.

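### The 80% power stated for the 3-month behavior score counts every randomised man, although the protocol expects one in five to be lost by then; at about 40 completers per arm it is about 71%

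*Protocol article*

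**What the plan says.** The Statistical Power section of the protocol article gives this power statement for the behavior score: "With 50 participants per group, there is 80% of power to detect an effect size of 0.57 at a 2-sided alpha of .05". The comparison is the change from baseline to 3 months in each of Levels 2, 3 and 4 against Level 1. A worked example follows. It supposes that "men in the reference group (Level 1) experience a 2-point increase in scores from baseline to 3 months", and finds at least 80% power if there is "an average increase of 4.85 points or greater in Level 2, with an SD of 5". Under Study Design and Setting, the target is 200 men split equally over four arms, so 50 per group is everyone randomised.

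The Acceptability and Feasibility section gives the expected retention: "We expect to retain 80% of the full sample postintervention (n=160) and 80% of the postintervention sample (n=128) at follow-up". The Statistical Power section also anticipates 80% retention at 3 months and carries the resulting count into its precision calculation for 6-month retention: "If we assume 160 individuals complete the 3-month surveys".

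The score is computed from self-reported survey data. Proposed Statistical Analyses announces an intent-to-treat analysis, and says that adjustment for baseline covariates will be considered.

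**The concern.** A man who does not complete the 3-month survey has no observed change score. The power statement for that score nevertheless uses the number randomised, while the paragraph just before it applies the expected loss to a different calculation. The two paragraphs therefore assume different numbers of men with 3-month data.

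What is at stake is how the three comparisons with Level 1 are read. A reader who takes the statement at face value will think that each has an 80% chance of detecting an effect of 0.57. Under the protocol's own retention figure, and with the unadjusted comparison that the statement describes, the chance is lower and the detectable effect is larger.

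**Working it through.** **Inputs from the protocol article**
- Randomised: 200 men in four equal arms, so 50 per arm (Study Design and Setting).
- Two-sided alpha 0.05, power 80%, effect size d = 0.57 (Statistical Power).
- Worked example: mean changes of 2 and 4.85 points, SD 5 (Statistical Power).
- Expected 3-month completers: 160 of 200 (Acceptability and Feasibility).

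**Assumption added here:** loss is equal across arms, so 160/4 = 40 completers per arm. The article gives only the total.

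**Method:** two-sample t-test with n per arm. Power comes from the noncentral t distribution with 2n − 2 degrees of freedom and noncentrality d × √(n/2).

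**Step 1. Reproduce the plan's figure.**
- The example is consistent with the effect size: (4.85 − 2)/5 = 2.85/5 = 0.57.
- At n = 50, the noncentrality is 0.57 × √25 = 2.85 and power is 80.6%. The normal approximation gives 81.3%.
- Solving for n at exactly 80% power gives 49.3 per arm. The effect detectable with 80% power at n = 50 is 0.566.

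The stated 80% is thus right for 50 evaluable men per arm, and almost nothing is left over to absorb loss.

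**Step 2. Apply the protocol's retention.**
- At n = 40, the noncentrality is 0.57 × √20 = 2.55 and power is 71.1%. The normal approximation gives 72.2%.
- The effect detectable with 80% power at n = 40 is 0.634. At SD 5 this is 0.634 × 5 = 3.17 points, so the example becomes 5.17 against 2.

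**Step 3. Test the equal-loss assumption.** With 45 completers in one arm and 35 in the other (80 in total, as before), power at d = 0.57 is 70.5%. Moderate imbalance changes little.

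**Step 4. Could baseline adjustment restore the figure?** Take the SD of 5 as that of the change score, and assume equal variances at the two times with baseline-to-3-month correlation ρ. The residual SD after adjusting for baseline is then 5 × √((1 + ρ)/2). The article gives no value for ρ, so a range is shown, for a difference of 2.85 points and 40 per arm:

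| Assumed ρ | Residual SD | Effect size | Power |
|---|---|---|---|
| 0.3 | 4.03 | 0.707 | about 88% |
| 0.5 | 4.33 | 0.658 | about 83% |
| 0.7 | 4.61 | 0.618 | about 78% |

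Adjustment can recover the loss, depending on ρ.

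**Step 5. Does analysing all randomised men restore the figure?** Only through some rule for the missing scores. As an illustration, set the change to zero for the missing 20%. The difference in means becomes 0.8 × 2.85 = 2.28. The variance in an arm with mean change m is 0.8 × 25 + 0.16 × m², which is 20.64 for m = 2 and 23.76 for m = 4.85. The average is 22.20, an SD of 4.71. The effect size is 2.28/4.71 = 0.484, and power at 50 per arm is about 67%.

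**The case against.** The strongest reply is that nothing has been miscalculated. The statement is conditional on 50 per group, and on that condition both the power and the example are correct. The effect size of 0.57 is not presented as a smallest important difference. It is close to what 50 per arm can detect, and the 2 points, 4.85 points and SD of 5 are offered as an example. On this view no design target is missed: the detectable effect moves from 0.57 to about 0.63, or about 0.3 points on a scale of 0 to 22. All of this stands. It makes the fault an inconsistency between assumptions, not a computing error.

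A second reply is that the analysis may not be an unadjusted comparison of completers. Intent-to-treat is stated, regression is among the methods listed, and the handling of missing scores may properly sit in an analysis plan that is not shown. This stands in part, since the 71% belongs to an unadjusted t-test on completers. But the power statement itself describes a plain comparison of change scores, covariate adjustment is only to be considered, and analysis by assigned arm does not supply missing 3-month answers.

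A third reply is that this is a pilot whose primary outcomes are accrual, recruitment and retention, with behavior change secondary and no allowance for multiple testing. That is correct and limits the importance of the point.

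A reader might be tempted to go further in three ways that the article does not support:
- It might be inferred that the trial's main efficacy test is underpowered. The article has no primary efficacy test.
- It might be inferred that power at 6 months is deficient too. The article makes no 6-month power claim for the score.
- It might be inferred that an effective level of support will be discarded after a null result. The article contains no rule that drops or adopts a level on a significance test.

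**Conclusion.** The point holds as a moderate internal inconsistency. The protocol article claims 80% power for a 3-month change score on all 50 randomised men per arm, yet expects 3-month data from 160 of 200. With an unadjusted two-sample t-test on about 40 completers per arm, power at an effect size of 0.57 is about 71%. The chance of missing such an effect in any one comparison is therefore about 29%, against the 20% implied. The effect detectable with 80% power is about 0.63, or about 3.2 points if the SD is 5.

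These figures rest on 80% retention, equal loss across arms (45 against 35 barely alters the result), the article's SD of 5 for the values in points, and an analysis without baseline adjustment. The finding concerns the accuracy of a stated property. It is not a reason to enlarge the trial, and it leaves the primary feasibility outcomes untouched.

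**What to change.** Rewrite the behavior-score paragraph of the Statistical Power section for about 40 completers per arm. State that this follows from 160 completers in total with equal loss across arms. Then give either 80% power for an effect size of about 0.63, or about 71% power for 0.57. Change the worked example to match: a 2-point rise in Level 1 against 5.17 points in Level 2 at SD 5, in place of 4.85.

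If the sponsor would rather base the claim on a baseline-adjusted analysis, the article should commit to that analysis instead of leaving adjustment open. It should also show power over a range of assumed baseline correlations, as in the table above, because no single value has a source in the article.

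The cost is one paragraph of text and a slightly less favourable figure. Enrolment, design and data collection stay as they are.
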